### Trial process and trial-specific training

2.11

All practices will receive two separate sets of training. First in relation to the conduct of the trial – the whole dental team including the receptionist, will receive training in Good Clinical Practice and trial procedures (e.g. patient consent, randomisation procedures and completing study records). A crib sheet detailing study procedures in all three arms will be provided for reference. Secondly, researchers will train dental teams in trial-specific processes including how to take (whole dental team) and clinically interpret (dentists only) QLF photographs, again supported by written information, and a video about the use of the camera. Both types of training will be undertaken in the dental practice itself. Given that research identifies that verbal metaphors can influence patients' mental images of their condition [44], trial specific training will include standard messages such as ‘*This red patch on the QLF photograph shows bacteria which have not been cleaned by you for 2–3 days. If you do not improve tooth-brushing here you are highly likely to develop problems’*.

### Data collection procedures

2.12

Data will be collected at baseline, then 2–3 weeks later when the patient returns for their first treatment visit (second dental visit, V2), and then at 5–6 weeks post intervention (third dental visit, V3), (Fig. 6, Table 1). Since eligible patients are those at medium/high risk of poor oral health, we expect the patient to need to return for further care, and so we will collect data opportunistically at this time. At these V2 and V3 follow up visits, the dentist will measure BPE (before the patient receives usual care treatment), and a further QLF photograph will be taken (not shown to the patient) to enable a change in plaque coverage and demineralisation to be measured from QLF images. Participants will be asked about any change in behaviour in relation to the messages (Fig. 3) listed on the printed cards (given to all patients at the first visit), using the item stem ‘*Since my last appointment I have* …. ’.

**Fig. 6 fig6:**
[figure not shown]
Study flow diagram.

**Table 1 tbl1:** Data collection schedule.

TIME POINTS	Baseline (Visit 1)	Visit 2	Visit 3	6-months	12-months
Collection method					
**Assessments – self report**					
Patient demographics	x				
REALM-R	x				
WTP	x				
Dental visiting history/experience	x				
Dental anxiety (MDAS)	x				
Self-assessed oral health	x	x	x	x	x
Oral health behaviours: toothbrushing, diet, fluoride and smoking	x	x	x	x	x
EPPM and behaviour change predictors	x	x		x	x
Patient/clinician communication (CAT)	x				
**Assessments – clinical**					
QLF photographs	x	x	x		
Number of natural teeth	x				
BPE	x	x	x		

There will be two further follow up points at 6 and 12 months post intervention, involving questions completed either by telephone or email, depending on what contact information the patient gave for this purpose. For those who cannot be contacted using this method, postal questionnaires will be sent. This will be conducted by a trained member of the research team. Patients who complete follow-up will be given the opportunity of being entered into a prize draw.

Measures will be collected according to the schedule outlined in Table 1. The patients will enter some data themselves using a Tablet computer with Qualtrics survey software (Version 092,017, ^©^ 2017 Qualtrics^®^). Trained dental nurses will administer an assessment of literacy (REALM), enter some demographic details and take QLF photographs.

#### Measuring WTP

2.12.1

This will be self-completed by patients on the Tablet PC platform, supported by a trained dental nurse, where required. The WTP elicitation will occur before the patient has been given risk information in any form; so all participants will give values for all three interventions, regardless of subsequent randomisation to one intervention. Participants will be given descriptions and sample images of the three interventions (Fig. 3, Fig. 4, Fig. 5), and asked to rank them in order of preference, and then asked firstly for their WTP for the lowest ranked intervention. This will be supported by a script which encourages realistic, budget constrained responses and which emphasises that the exercise is about value rather than price.

On the computer participants will be presented with a series of virtual cards with different values from 50 pence to £150 on them and asked to drag each card to one of three boxes: “*Would pay; Wouldn't pay; Not sure”.* The different valued cards will be presented in a random order, with a random starting card. Participants will not see the value of subsequent cards until the current card has been placed. Once all cards have been placed, the lowest “*Wouldn't pay*” and highest “*Would pay*” value will be shown, and the participant asked for a maximum WTP value in an open-ended format. This shuffled payment card approach to WTP elicitation is thought to reduce starting point and range bias found in WTP methods [45].

Once a WTP value for the lowest ranked intervention has been determined, participants will then be asked what extra they would be willing to pay for their next most preferred intervention in an open-ended question. Finally, participants will be asked what extra they would be willing to pay on top of their value for their middle-preferred intervention. This incremental approach to eliciting WTP has been shown to give more robust valuations [46].

After receiving information at their check-up, patients will return to the Tablet PC-based task, where they will be reminded of the WTP value they had given prior to the intervention which had been allocated to receive. They will then be asked if they would revise their WTP, given their actual experience with that form of information. If they indicate they would revise this, the new value will be collected using an open-ended question.

### Analysis plan

2.13

A detailed statistical analysis plan will be prepared prior to data analysis.

#### Analysis of WTP

2.13.1

We will compare hypothetical WTP across the whole sample, across the three arms. We will also compare hypothetical WTP with WTP for a good that has been “consumed” by comparing WTP before and after receiving the information form in that arm. WTP data will be analysed both descriptively, comparatively and econometrically. Descriptive data analysis will consist of WTP value means with standard deviations, along with medians and quartiles for each information form. The WTP values for each system will be compared using appropriate comparative tests (e.g. most likely to be Mann Whitney U tests given the likely distribution). In order to understand fully how various dental and demographic factors influence values (WTP), econometric regression analyses will be carried out.

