
### Sample size calculation

2.10

The required sample size calculation is based on a need to detect significant differences in the primary outcome (WTP) between the two interventions (Traffic Light and QLF) and usual care arms at 80% power with α = 0.05. Sample sizes for WTP studies are recognised as difficult, given the problems in deciding on a minimally important difference amongst others [42]. Moreover, for this study, no previous WTP valuations have been undertaken for similar “goods” i.e. information based “goods” in health. In the absence of reliable standard deviation and effect size estimates, sample size was calculated with effect sizes based on numbers of standard deviations rather than absolute numbers. Thus, to detect a difference of 0.5 standard deviations 63 people is calculated to be required per arm. To detect 0.33 standard deviations, 145 per arm would be needed. Accepting a detectable difference between half and a third of a standard deviation and allowing for around 20% refusal to answer WTP questions (protest responses) gives a figure of 133 in each arm or a total sample size of 400. We then calculated the implication of this sample size for the detection of clinical outcome effects, and based this on the secondary outcome of PPI, measured using QLF [35]. Published data on a group of 38 college students showed a mean PPI of 14.8, with a standard deviation of 7.7 [43]. As this is likely to be a more homogenous population than our study, a more conservative estimate of standard deviation of 10 has been used to calculate a sample size of 133 per group would allow us to detect a mean different of 3.5 in PPI between groups, with 80% power, at the 0.05 significance level.

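### Each participant values all three information forms, yet the test indicated for the primary WTP outcome (Mann-Whitney U) treats the values as independent samples, and the comparison across arms is left ambiguous

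*Protocol article*

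**What the plan says.** Under Measuring WTP (2.12.1), the values are elicited ahead of any risk information, and the section draws the consequence: "so all participants will give values for all three interventions, regardless of subsequent randomisation to one intervention". Participants rank the three forms and value the lowest ranked. They then say how much extra they would pay for the next form, and how much extra again for the top one. After the consultation they may revise only the value for the form they received.

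Under Analysis of WTP (2.13.1), the first comparison is stated as: "We will compare hypothetical WTP across the whole sample, across the three arms". Values for each form are then to be "compared using appropriate comparative tests (e.g. most likely to be Mann Whitney U tests given the likely distribution". The section also plans a before-and-after comparison for the form received, means with standard deviations, medians with quartiles, and regression analyses.

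The Sample size calculation (2.10) frames the primary comparison as one "between the two interventions (Traffic Light and QLF) and usual care arms". The error rates are set "at 80% power with α = 0.05". The step for half an SD reads "to detect a difference of 0.5 standard deviations 63 people is calculated to be required per arm". For a third of an SD the section says "To detect 0.33 standard deviations, 145 per arm would be needed". The last step, which arrives at 400 patients, is "allowing for around 20% refusal to answer WTP questions (protest responses) gives a figure of 133 in each arm or a total sample size of".

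The Analysis plan (2.13) says a detailed statistical analysis plan will be prepared before data analysis.

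**The concern.** The data collection makes pre-information WTP a within-person outcome. Three values come from one person, and the second and third are built on the one before. The sample size, the description of the comparison and the indicated test all treat it as a between-group outcome. The reason given for Mann-Whitney U is the likely distribution. Skewed data justify a rank method, but for linked values that means a paired one, such as Wilcoxon signed-rank or Friedman.

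The second difficulty is what is being compared. The wording puts the whole sample and the three arms in the same sentence, and these lead to different analyses. WTP is the primary outcome and measuring preferences is the first objective. If this section is carried into the analysis plan as it stands, the primary test could miss small but real preferences that the data could show.

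**Working it through.** **Inputs.** From 2.10: α = 0.05 (two-sided reproduces the stated figures), power 80%, target differences 0.5 and 0.33 SD, 133 per arm, 400 in total, about 20% refusals. Respondents: 400 × 0.8 = 320 overall, and 133 × 0.8 ≈ 106 per arm. The within-person correlation ρ between two forms is not in the document, so it is assumed to lie between 0.3 and 0.8. The 0.15 SD difference used below is also an assumption, chosen to show where the tests diverge.

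**Step 1: reproduce the stated sample size.** Two independent means: n per arm = 2 × ((1.96 + 0.84)/d)².
- d = 0.5: 62.8, so 63, as stated.
- d = 0.33: 144.1, so 145, as stated.
- With 106 respondents per arm the detectable difference is 2.80 × √(2/106) = 0.385 SD, between a third and a half SD as the protocol accepts.

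The figures are correct for independent arms, and only in that sense.

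**Step 2: forms compared over the whole sample.** With n = 320, an independent-samples test uses a standard error of √(2/n) SD. The true standard error of the difference is √(2(1−ρ)/n) SD. The true size is therefore 2 × P(Z > 1.96/√(1−ρ)):
- ρ = 0.3: 1.96/0.837 = 2.34, giving 1.9%.
- ρ = 0.5: 1.96/0.707 = 2.77, giving 0.56%.
- ρ = 0.8: 1.96/0.447 = 4.38, giving 0.001%.

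Simulation of the rank tests on 320 pairs agrees:

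| ρ | Mann-Whitney size | Signed-rank size | Mann-Whitney power, 0.15 SD | Signed-rank power, 0.15 SD |
|---|---|---|---|---|
| 0.3 | 2.2% | about 5% | 44% | 60% |
| 0.5 | 0.5% | about 5% | 43% | 74% |
| 0.7 | 0.05% | about 5% | 42% | 93% |
| 0.8 | about 0% | about 5% | 42% | 98% |

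Repeat simulations differ by two or three percentage points.

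At the protocol's 0.33 SD the loss disappears. For ρ = 0.3, the least favourable case in the range, √(2/320) = 0.0791. The unpaired test's power is P(Z < (0.33 − 1.96 × 0.0791)/(0.0791 × 0.837)) = P(Z < 2.65), about 99.6%. The paired test is higher still.

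In terms of what the trial could detect with 80% power, a paired analysis reaches 2.80 × √(2(1−ρ)/320). This is 0.185 SD (ρ = 0.3), 0.157 (0.5) and 0.099 (0.8), against 0.385 SD for the comparison of independent arms.

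**Step 3: each arm contributes only its own form.** The samples are independent and Mann-Whitney U is valid, but two of the three values per person are unused. Simulated power with about 106 per arm is roughly 63% to 65% at 0.33 SD, 79% at 0.385 SD and 19% at 0.15 SD.

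**Step 4: the same form's pre-information value compared between randomised arms.** The value is given before the allocation is revealed, so the arms cannot differ except by chance. Rejection is about 5% whatever patients prefer.

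**The case against.** Several points on the other side stand.

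- **The test is not fixed.** It is offered as an example and as the most likely choice, with a detailed analysis plan to follow. It is a poor indication, not a final commitment.
- **At the design effect the choice hardly matters.** For 0.33 to 0.5 SD over 320 respondents, both tests are almost certain to detect the difference. The loss appears only at smaller differences, which the protocol does not target.
- **The means are covered.** Section 2.13.1 already reports mean WTP for each form, so a cost-benefit analysis does not depend on the rank test.

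A reader might also infer stronger conclusions that the document does not support.

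- **That the comparison across arms tests nothing.** This is true only of the reading in Step 4. The word arms may simply mean the three forms, since later sentences refer to each form or system. The own-form reading is valid and fits the per-arm sample size.
- **That false positives are inflated.** With positive correlation the error runs the other way.
- **That the trial is too small.** A paired analysis is better powered than the stated calculation.
- **That a randomised comparison of WTP has been wrongly omitted.** The stated objective is to measure preferences, and the design deliberately elicits them before information is given. A between-arm analysis of the revised value would be informative but is optional.
- **That WTP is elicited before randomisation.** Section 2.7 places randomisation just after enrolment, with the envelope opened later, while 2.12.1 calls randomisation subsequent. The safe statement is that values are given before the allocation is revealed.

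**Conclusion.** The concern holds in a limited form. Sections 2.10 and 2.13.1 handle a within-person primary outcome as if it came from independent groups, and 2.13.1 does not say which comparison is meant. On the whole-sample reading, the indicated test is conservative and loses power for small differences: about 42% to 46% against about 60% to 99% at 0.15 SD. On the own-form reading it is valid but discards two thirds of the values. On the same-form reading it cannot inform preference.

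The sizes rest on an assumed correlation of 0.3 to 0.8, on 320 respondents, and on normal data in the simulations. A positive correlation is plausible because the values are increments from one person, but the document gives no figure. If the correlation were near zero, the two tests would perform alike. This should be fixed. It does not threaten the trial, because the direction is conservative and the effect at the design difference is negligible.

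**What to change.** In 2.13.1, and in the analysis plan that follows it:

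1. State the primary contrasts as the within-person differences TL minus V and QLF minus V in pre-information WTP, over all respondents.
2. Name a paired method in place of Mann-Whitney U: Wilcoxon signed-rank, or the mean paired difference with a bootstrap confidence interval that resamples participants.
3. Replace the sentence about the whole sample and the three arms with one that says which comparison is meant, and do not test the same form's pre-information value between randomised arms.
4. Optionally, add a between-arm analysis of post-information WTP for the form received.

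The cost is a change of wording. No new data and no larger sample are needed; the existing sample size becomes more than adequate for the contrasts as restated.

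### The test named as most likely for comparing WTP between the three forms (Mann-Whitney U) is for independent samples, but each participant values all three forms

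*Protocol article*

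**What the plan says.** WTP is the primary outcome (Protocol article, 2.8.1). Section 2.12.1 has it elicited before any risk information is given, "so all participants will give values for all three interventions, regardless of subsequent randomisation to one intervention". Participants rank the forms and value the lowest-ranked one. They are then "asked what extra they would be willing to pay for their next most preferred intervention in an open-ended question", and after that for a further extra for the top-ranked form. After the check-up they are reminded of their earlier value for the allocated form and may revise it.

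Section 2.13.1 opens: "We will compare hypothetical WTP across the whole sample, across the three arms". It adds a second comparison, "comparing WTP before and after receiving the information form in that arm". It then says that the values for each form will be compared by suitable tests, giving as an example that they are "most likely to be Mann Whitney U tests given the likely distribution". No paired test or within-person model is named for either comparison. Section 2.10 sizes the trial on WTP as a comparison of separate arms, the two interventions against "usual care arms at 80% power with α = 0.05". Section 2.13 says that a detailed analysis plan will follow.

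**The concern.** Mann-Whitney U assumes two independent samples. The V, TL and QLF values come from the same people, and the elicitation makes them share each person's base value. Differences between people in income and budget cancel when one person's values are subtracted, but they stay in the variance that an unpaired test uses. The reason given for the test is the shape of the distribution. That argues for ranks over means and does not address pairing.

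The wording about arms adds to the problem. Hypothetical WTP is collected before any information is given, so randomised arms compared on the same form's pre-information value could differ only by chance. What is at stake is the calibration of the primary p-values and the precision that the design gains by asking everyone about all three forms.

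**Working it through.** **Inputs.** From 2.10: alpha 0.05, power 80%, targets 0.5 SD and 0.33 SD, about 20% protest responses, 400 patients. Sidedness is not stated; two-sided reproduces the figures. The SD of WTP and the within-person correlation (rho) are not given, so rho is varied as an assumption.

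**The plan's own figures.** For independent groups, n per arm = 2(1.96 + 0.8416)²/d² = 15.70/d².
- d = 0.5: 62.8, so 63.
- d = 0.33: 144.1, so 145.
- 133 per arm less 20% leaves about 106, and √(15.70/106) = 0.385 SD, inside the stated range of a third to a half SD.

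The figures reproduce, as a two-independent-groups calculation.

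**Usable responders in the whole-sample comparison.** 400 × 0.8 = 320, each giving three values.

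**Size of the unpaired test on paired values.** This is normal theory, standing in for the rank test. In SD units the unpaired standard error is √(2/320) = 0.0791. The true standard error of the within-person difference is √(2(1 − rho)/320). The ratio is 1/√(1 − rho), and the true size of a nominal 5% test is 2·P(Z > 1.96/√(1 − rho)).

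| rho | SE ratio | true size |
|---|---|---|
| 0 | 1.00 | 5.0% |
| 0.3 | 1.20 | 1.9% |
| 0.5 | 1.41 | 0.6% |
| 0.7 | 1.83 | 0.03% |

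**Power with 320 responders (unpaired vs paired).**

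| difference | rho 0.3 | rho 0.5 | rho 0.8 |
|---|---|---|---|
| 0.10 SD | 20% vs 33% | 16% vs 43% | 6% vs 81% |
| 0.20 SD | 75% vs 86% | 79% vs 95% | 90% vs >99% |
| 0.33 SD | >99% both | >99% both | >99% both |

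Worked cell, 0.10 SD at rho 0.5: the true standard error is 0.0559 and the unpaired critical difference is 1.96 × 0.0791 = 0.155. Unpaired power is P(Z > (0.155 − 0.10)/0.0559) = P(Z > 0.98) = 16%. Paired power is P(Z < 0.10/0.0559 − 1.96) = P(Z < −0.17) = 43%. At 0.33 SD the lowest unpaired power is 98.7%, at rho 0.

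**Rank tests on the actual elicitation.** A simulation (500 runs per setting, n = 320) assumed base values lognormal with median £10 and log SD 1, 15% set to zero; exponential extras, 30% of them zero; and 60% of people preferring QLF to V.

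| mean non-zero extra | Spearman rho | Mann-Whitney rejects | signed-rank rejects |
|---|---|---|---|
| £5 | 0.79 | 2% | 76% |
| £10 | 0.60 | 23% | 74% |
| £20 | 0.39 | 48% | 74% |

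With no preference, Mann-Whitney rejected in 0 to 1.2% of runs and signed-rank in 4 to 5%. These settings are small differences. The mean QLF minus V gap is (0.6 − 0.4) × 4/3 rank steps × 0.7 × mean extra, or £0.93, £1.87 and £3.73. Against simulated SDs of about £21.5, £23.7 and £30.4, that is 0.04, 0.08 and 0.12 SD.

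**The case against.** **The test is not fixed.** It is offered as an example of a suitable test, doubly hedged, and a detailed plan is to follow. A paired rank test would already comply. This stands, and it limits the severity. But it is the only test named for the primary outcome, and a plan that followed the wording would carry the mismatch forward.

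**The comparison may be between arms.** Section 2.10 sizes arms and 2.13.1 mentions arms. If only each arm's own allocated form were compared, the samples would be independent and Mann-Whitney U valid. That reading fits poorly with a whole-sample comparison of values that everyone gives, and it would leave two thirds of the elicited values unused. With about 106 valid responders per arm, power at 0.2 SD would be about 31%, against 95% paired at rho 0.5. A between-arm comparison of experienced WTP is different: each person re-values only the allocated form, so an unpaired test is right there.

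**The planned effect would be found anyway.** This stands in full. A reader might infer that the trial could miss a preference of the size it was designed for, or that most of its power is lost. The power figures do not support that at 0.33 SD or above.

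**The error is in the safe direction.** With positive correlation it does not raise the false-positive rate. It costs sensitivity and calibration.

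**Conclusion.** The point holds as a mismatch between the illustrative test and the within-person design. The direction is conservative given positive correlation, which the incremental elicitation makes very likely. The amount depends on a correlation that the document does not give: modest near 0.3, severe at 0.7 or above. The practical loss is confined to differences of about 0.2 SD or less. Such differences cannot be ruled out, because 2.10 says that there are no earlier valuations of comparable information goods and no reliable effect size.

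Two stronger readings are not supported. One is that the p-values are far too large whatever the data: that needs a high correlation, which is an assumption. The other is that the protocol assigns Mann-Whitney U to the before-versus-after comparison: its test sentence concerns values for each form, and no test is named for before versus after. The calculations rest on 320 responders, normal theory and, in the simulation, assumed WTP amounts.

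**What to change.** In 2.13.1:

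1. For hypothetical WTP, replace the reference to the three arms with the three forms, within participant.
2. Replace Mann-Whitney U with one pre-specified paired analysis of TL minus V and QLF minus V in everyone with valid WTP. For example, make the Wilcoxon signed-rank test primary, with a bootstrap interval for the mean paired difference as a supporting estimate. The two target different quantities, so state which is primary.
3. State a paired analysis for before versus after WTP.
4. In any regression pooling the three values, use a participant random effect or participant-clustered standard errors.
5. Keep an unpaired test only for a between-arm comparison of experienced WTP for the allocated form, if that is intended.

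The cost is wording in 2.13.1 and the analysis plan. No new data and no more patients are needed.
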